## Abstract

**Background:**

Schizophrenia and bipolar disorder are severe mental illnesses that can have a significant disabling impact on the lives of people. Psychosocial interventions that stress hope and recovery as a part of a multi-dimensional approach are possibly indicated to support people with severe mental illness in facilitating recovery. Illness Management and Recovery (IMR) is a curriculum-based psychosocial intervention designed as structured program with a recovery-oriented approach. The aim of IMR is to rehabilitate people with severe mental illnesses by helping them acquire knowledge and skills in managing their illness and achieve personal recovery goals. Previous randomised clinical trials indicate that IMR can be implemented with a good effect and a high fidelity though further trials are crucial to demonstrate the potential effectiveness of IMR.

**Methods/Design:**

The trial design is a randomised, assessor-blinded, multi-centre, clinical trial of the IMR program compared with treatment as usual for 200 participants diagnosed with schizophrenia or bipolar disorder under the care of two community mental health centres in the Capital Region of Denmark. The primary outcome is level of functioning at the end of treatment. The secondary outcomes are disease symptoms; use of alcohol/drugs; individual meaning of recovery; hope; hospital admissions and out-patient psychiatric treatment at the end of treatment and the abovementioned and level of functioning at follow-up 21 months after baseline.

**Discussion:**

If the results of this trial show IMR to be effective these positive results will strengthen the evidence of IMR as an effective comprehensive psychosocial intervention with a recovery-oriented approach for people with severe mental illness. This will have significant implications for the treatment and recovery of people with severe mental illness.

**Trial registration:**

Registration number NCT01361698.

## Background

Schizophrenia and bipolar disorder are severe mental illnesses that impact people's lives in many disabling aspects. Research indicates that medication alone is not sufficient to help people with these diagnoses but has to be a part of a multi-dimensional approach complemented with evidence-based psychosocial interventions in a more comprehensive rehabilitation model [1,2]. Psychosocial interventions that stress coping and personal goals may contribute to facilitating recovery from the profound functional and social deficits characterising people with schizophrenia and bipolar disorder [3-5].

A recovery-oriented approach to these severe mental illnesses holds that individuals are more than the sum of their symptoms and that recovery involves a redefinition of one's illness as only one aspect of a multi-dimensional sense of self [6].

Illness Management and Recovery (IMR) is a curriculum-based, standardized program based on a recovery-oriented approach to rehabilitation for people with severe mental illnesses. The program is designed by [name] et al. as an evidence-based practice based on the principles of recovery to help people with severe mental illnesses to set individual meaningful goals for their lives and gain illness self-management skills and thereby contribute to their individual recovery-process [7]. By collecting the evidence of different empirically supported practices including psycho-education, relapse prevention, behaviour training to improve medication adherence, coping skills training and social training, IMR was developed as a full-ranged rehabilitation program and consolidated into a single standardised program for study and dissemination.

The theoretical foundation for the IMR program is the trans-theoretical model and the stress-vulnerability model. The trans-theoretical model assumes that human change developed over a series of stages and by motivating people in the stage they are in through the IMR program they can easier succeed in achieving their own personal recovery goals [8,9]. The stress-vulnerability model builds on the assumption that the course of severe mental illness is determined by an interaction of biological vulnerability, stress and coping. The aim of IMR is to interrupt the circle of stress and vulnerability that leads to poor functioning and relapse [10,11], see Figure 1.

**Figure 1 F1:**
[figure not shown]
**The theoretical foundation for Illness Management and Recovery**. The trans-theoretical model and the stress-vulnerability model are the theoretical underpinning of the IMR program.

The core values of IMR are hope, personal choice, collaboration, respect, and recognizing people as experts in their own experience of mental illness. First and foremost, the process of teaching Illness Management and Recovery involves conveying a message of hope and optimism, so that people with mental illness believe that they can reach their own goals and begin a progress of recovery. Non-controlled studies of IMR have provided some support for the effectiveness and feasibility of the program [12-14]. The effectiveness has been tested in a few randomised trials with various settings [15-18] and these trials indicate that IMR in group level can be implemented with a good effect and a high fidelity to the program curriculum [19,20]. Due to methodological limitations in the previous trials regarding the blinding process, follow-up assessments and the power of the sample size further trials are crucial to prove the effect.

In the present IMR trial, the following alternative hypotheses will be tested: Patients in the IMR program will have improved at least 6 points on the Global Assessment of Function scale (GAF-F) compared with patients receiving treatment as usual at follow-up 9 months after baseline. Furthermore, the participants in the IMR program will show a greater improvement after 9 months in relation to symptoms, drug/alcohol addiction, relapse, rehospitalisation and treatment, knowledge about their mental disease, coping strategies, recovery and hope. Moreover the difference between the intervention groups will be sustained 21 months after baseline.

## Methods/Design

The trial design is a randomised, assessor-blinded, multi-centre, clinical trial of the IMR program compared with treatment as usual in 200 participants diagnosed with schizophrenia or bipolar disorder under the care of two community mental health centres in the Capital Region of Denmark.

From January 2011 to December 2013 IMR will be tested in two community mental health centres with the participation of 200 patients. The duration of the trial will be four years. Recruitment to the trial has begun in January 2011 and is due for completion in February 2012. The intervention will start March 2011 and the follow-up assessments in November 2011. The participants will take part in the trial for the baseline interview, and for the follow-up interviews by 9 and at 21 months (one year after the intervention is ended). Moreover a naturalistic follow-up is planned in a period of ten years to evaluate any long-term effects. After the 21 months of follow-up the patients allocated to the control group will be offered IMR, if the program is shown to be effective.

### The experimental intervention

Patients randomised to the experimental intervention will be offered IMR plus 'treatment as usual'. The details of the IMR program has been described elsewhere [21], but will be briefly outlined below. The program is organised into 11 curriculum topic areas: recovery strategies, practical facts about mental illness, the stress-vulnerability model, building social support, using medication effectively, drug and alcohol use, reducing relapses, healthy lifestyle, coping with stress, coping with problems and symptoms, and getting your needs met in the mental health system. The first topic area is an explanation of the concept of recovery followed by an identification of personal recovery goals related to the individuals' own meaning of recovery. While the first 10 modules have been part of the IMR manual [22] from the start, the 11th module on healthy lifestyle is added later and has not been tested previously. We include this module in the IMR program on the recommendation of the founders of the program (personal communication with [name], Dartmouth University, USA).

IMR can be provided in an individual or group format, and generally lasts between four and ten months with a series of weekly sessions where mental health practitioners help the participants to develop personalized strategies for managing their mental illness and moving forward in their lives. Every session has the same routine, which means that the whole program is following a structured pattern. The curriculum topic areas are taught by IMR facilitators using a combination of educational, motivational, and cognitive-behavioural teaching strategies and homework assignments developed collaboratively with the participant. With the participants' consent, significant others (e.g. family, friends) are encouraged to be involved in helping participants learn self-management strategies and pursue their personal goals. In the program the participant's individual goals are often broken down into smaller steps to facilitate a continuously progress towards achieving the goals.

In this Danish trial IMR will be implemented in group format with 10 patients assigned to each group and two IMR facilitators, and the IMR program will require nine months of weekly sessions to complete. The curriculum of IMR has been translated into Danish prior to the intervention.

To ensure the fidelity of the intervention at the community mental health centres the IMR facilitators will:

■ Be experienced mental health clinicians with all together at least four days course in teaching IMR. The teaching will be given prior to the intervention, and again after six months and if need again after one year by a well-experienced IMR educator from USA (The Mental Health Center of Greater Manchester, New Hampshire).

■ Receive supervision from the well-experienced IMR educator via an Internet connection to begin with every second week and later on once a month.

■ Be involved in a network group for all IMR facilitators, formed to support the implementation of IMR in the two community mental health centres.

■ Be evaluated by a trained IMR facilitator from the other community mental health centre halfway through each IMR course using the IMR Fidelity Scale. The IMR Fidelity Scale consists of 13 items that are rated on a 5 point scale [22].

### The control group

Patients randomised to the control group will get 'treatment as usual' only. This means individual adapted interdisciplinary treatment including medication, individual support, occupational therapy, psycho-education and group therapy. Some of the staff members that also are IMR facilitators have the role of being primary care provider both for participants in the IMR intervention and in the control group. To ensure that the staff members are following the principles of treatment as usual when meeting patients in the control group, they can consult a task force consisting of a well-experienced psychiatrist only performing treatment as usual.

### Inclusion and exclusion criteria

Eligible participants will be adults (age 18+) of both sexes who are: 1) associated with one of the two participating community mental health centres; 2) diagnosed following the ICD-10 criteria of schizophrenia or bipolar disorder; 3) able to speak and understand Danish; 4) giving informed consent verbally and in writing.

Patients will be excluded if they have: 1) a guardian or a forensic psychiatric arrangement; 2) comorbidity with the ICD-10 criteria of the diagnoses of dementia or mental retardation; 3) a large-scale substance abuse - if later on the abuse is under control, inclusion in the trial will be possible; 4) a current home of supported housing - since the treatment as usual given to this group of patients is significant different from patients living independently; 5) a current involvement in a psycho-educational course - patients are eligible for participation in the trial after the psycho-educational course has ended if they meet the inclusion criteria at this point; 6) not given informed consent.

### Recruitment and randomisation

Patients will be recruited from two community mental health centres in the Capital Region of Denmark: Frederiksberg-Vanløse and Ballerup-Egedal-Herlev, respectively. Each potential participant is interviewed with the diagnostic tool Present State Examination by a psychiatrist or a trained psychologist to evaluate whether the patient meets the criteria of diagnosis. After informed consent is obtained for each eligible patient the baseline assessments will be conducted. After baseline assessments the participants will be randomly allocated to either IMR or continue with treatment as usual. To secure concealment of the allocation sequence the randomisation will be central and telephone-based through The Copenhagen Trial Unit. The allocation sequence will be computer-generated, using permuted blocks of a varying block size with equal allocation to the two arms. The allocation sequence is stratified by diagnosis and community mental health centre.

### Participant withdrawal

If the participant decides to withdraw from the trial they can 1) participate in the baseline interview and then withdrawal from the treatment but participate in the follow-up interviews; 2) participate in the baseline interview and then withdrawal from the treatment and not participate in the follow-up interviews 3) withdraw from the whole trial so that all data about them are deleted.

### Assessments

At baseline, the participants' socio-demographic information on education, employment, marital status, clinical diagnosis, suicide attempts, and earliest contract with psychiatric services will be collected.

### Primary and secondary outcome measures

The primary outcome of the trial is overall functioning measured by Global Assessment of Function (GAF-F) post-intervention - after nine months. The GAF scale [23] can be divided into two scales GAF-F and GAF-S (one that focuses on functioning and one that focuses on symptoms) [24]. In this trial the focus of the primary outcome is functioning which is why the GAF-F scale is used. Information about the participant's level of functioning will be obtained from interviews with participants at baseline and follow-up.

The secondary outcomes include level of symptoms, social functioning, personal recovery experience and hope, substance abuse, use of services and suicide attempts. This information is obtained through an interview with an assessor blind to the allocation. The participant fill in questionnaires about their personal recovery and hope, the primary care provider (not blinded to the allocation) fill in a questionnaire about substance abuse, adverse events, and suicide attempts. Information about service use is obtained trough the hospital records. The measurements are chosen according to a well-known distinction between clinical recovery and personal recovery [25,26]. Clinical recovery refers to the absence of symptoms, an improvement in functioning and prolonged remission. Personal recovery refers to living a fulfilling and hopeful life even with limitations caused by illness. In this trial we have divided the assessments of recovery in accordance with these two perspectives.

### Clinical recovery

All outcome measures to assess clinical recovery are continuous scales. The overall level of symptoms is assessed by the subscale of symptoms of the global measurement Global Assessment of Function - Symptoms (GAF-S) [24]. The Positive and Negative Syndrome Scale (PANSS) [27] assesses the level of an severity of positive and negative symptoms as well as the general psychopathology. This scale is primary developed to measure symptoms of people diagnosed with schizophrenia but can be useful to people diagnosed with bipolar disorder as well [28]. The scale is a 7-point rating instrument that consists of 30 items.

Hamilton Rating Scale for Depression scale assesses the level of symptoms of depression. In this trial we use the version of the scale that includes 6 items referred to as Ham D_6 _[29]which is covering the core symptoms of depression.

Young Mania Rating Scale (YMRS) [29,30] is an instrument developed to rate severity of manic episodes. The YMRS consists of 11 items and a severity rating is assigned to each rating.

Personal and Social Performance (PSP) [31] is a scale developed from the Social and Occupational Functional Assessment Scale (SOFAS) to assess psychiatric patients level of functioning [32]. The scale assesses four domains of social functioning: socially useful activities, personal and social relationships, self-care and disturbing and aggressive behaviour. Besides giving more detailed and varied information about the participants' level of function, the PSP scale is used to secure the reliability of the GAF score.

### Personal recovery

Participants are answering questionnaires to assess aspects of their personal recovery this includes continuous scales of recovery, illness management, hope and satisfaction with psychiatric services.

Illness Management and Recovery Scale (IMR Scale) is a scale especially developed to the IMR program [33]. It summarizes different areas in 14 items relevant to the recovery process including personal goals, knowledge about the illness, admissions, use of alcohol or drugs, functioning, symptoms, stress and coping. The IMR Scale exists in two separate versions: one for the patient and one for the primary care provider.

Mental Health Recovery Measure (MHRM) [34] is a measurement of recovery in a general level and not specific attached to the IMR program. MHRM includes different aspects related to the process of personal recovery. It is a 30-item self-report scale designed to assess the recovery process for people with severe mental illnesses e.g. schizophrenia and bipolar disorder.

The Adult State Hope Scale [35] is a self-report scale of hope and optimism. It consists of 6 items and is rated on a scale from 1 to 8. The scale was psychometrically tested in college students and in a community sample, but has also been shown to be appropriate for people with severe mental illnesses as well [36].

Clients Satisfaction Questionnaire [37] assesses the participants' satisfaction with the psychiatric services. This information is relevant from both groups point of views since satisfaction with services can explain eventual drop out and the level of effect on the other measures. The satisfaction of the clients also gives indications of how the mental health community should look like in the future according to its users.

### Blinding

Assessments regarding clinical recovery will be conducted by an assessor blind to treatment allocation. The assessor will go through a profound assessment training program. Issues concerning inter-rater reliability will have no bearing on this trial since only one person will be conducting the assessments. Due to the nature of the intervention neither participants nor staff can be blinded to allocation, but are strongly inculcated not to disclose the allocation status of the participant at the follow up assessments. An employee outside the research team will feed data into the computer in separate datasheets so that the researchers can analyse data without having access to information about the allocation.

### Monitoring for participant compliance

The use of treatment is registered for both the experimental intervention group and the control group. This is done to ensure the similarity of the treatment as usual that both groups are offered. The attendance at the IMR sessions is registered to monitor the participation compliance. All information regarding covariates, primary outcome, secondary measures, use of psychiatric service and attendance at the IMR sessions is recorded in a case record form. A view of the data collection is listed in table 1.

**Table 1 T1:** Data collection

Source of collection	Assessments	Time of recording		
		
		Baseline	9 months (post intervention)	21 months (one year follow up)
Obtained trough Interview	Global Assessment of Functioning (GAF-F and GAF-S)	X	X	X
	
	Personal and Social Performance (PSP)	X	X	X
	
	Positive and Negative Syndrome Scale (PANSS)	X	X	X
	
	Hamilton Rating Scale for Depression (HAM-D6)	X	X	X
	
	Young Mania Rating Scale (YMRS)	X	X	X

Primary treatment provider fill out questionnaires	Alcohol and drug consumption	X	X	X
	
	Diagnose	X		
	
	First contact with psychiatric service	X		
	
	Suicide attempts	X	X	X
	
	Marital status	X		
	
	Housing condition	X		
	
	Education	X		
	
	Employment	X	X	X
	
	Use of treatment as usual		X	X
	
	IMR attendance - only for intervention group		X	X
	
	Life-threatening conditions (other than suicide)		X	X
	
	Illness Management and Recovery Scale - staff version	X	X	X

Patient fill out questionnaires	Illness Management and Recovery Scale - patient version	X	X	X
	
	Mental Health Recovery Measure	X	X	X
	
	Adult State Hope Scale	X	X	X
	
	Clients Satisfaction Questionnaire	X	X	

Hospital records	Suicide		X	X
	
	Death (all causes)		X	X
	
	Number of hospital admissions		X	X
	
	Length of hospital admissions		X	X
	
	Use of out-patient services		X	X

## Analysis

### Power and sample size

We are planning a trial of the continuous response variable, GAF-F, from independent control and experimental participants with one control per experimental participant. A previous study involving psycho-education in a Danish community mental health centre showed that response within each participant group was normally distributed with a standard deviation of 15 [38]. In the few previous studies using IMR or elements of IMR the effectiveness has been assessed by using the total GAF score showing a difference of 6-10 points [21,39]. Based on this knowledge we will conservatively estimate the true difference in the experimental and control group means to be 6 points on the GAF-F score. Using this estimation will require a total of 200 participants to reject the null hypothesis that the population means of the experimental and control groups are equal with probability (power) 0.8. The type I error probability associated with this test of the null hypothesis is 0.05. The power and sample size calculations have been made using the PS Power and Sample Size Calculations program version 3.0.34 [40].

The power of some the secondary measures has also been estimated with a total number of 200 participants. This showed that a sample size of 200 participants is sufficient to show a relevant effect size in PSP, PANSS and the IMR Scale corresponding to similar studies, see table 2. The remaining secondary measures have not been tested due to the fact that similar trials with these outcomes could not be obtained. Thus, the results of these analyses should be interpreted with caution, and the analyses should be considered as exploratory.

**Table 2 T2:** Power calculations of PSP, PANSS and IMR Scale

Measure	The level of significance	Power	St. deviation in a similar study	Effect size in a similar study	Minimum sample size	Reference
PSP	0,05	0,8	14	7	128	*Nasrallah et al. 2008 *[40]

PANSS	0,05	0,8	11	5	154	*Fowler et al. 2009 *[41]

IMR scale	0,05	0,8	0,5	0,41	48	*Hasson-Ohayon et al. 2007*[17]

Note: PSP: Personal and Social Performance; PANSS: Positive and Negative Syndrome Scale; IMR Scale: Illness Management and Recovery Scale.

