## Data analysis

The analysis will be performed by using the IBM SPSS Statistics version 19 for Windows. The data analysis will be based on the principle of intention-to-treat. The significance level for the analysis of the primary outcome and the secondary outcome will be 0.05.

Demographic variables will be listed in a table. The primary outcome measure is the continuous measurement GAF-F. The primary analysis of effectiveness will compare GAF-F at 9 months. The secondary analysis will compare effectiveness of the secondary outcome measures at 9 months and GAF-F and the secondary outcomes at 21 months. The analysis of differences between groups will be conducted using t-tests and analysis of the variances will be conducted using ANOVA. Repeated measures techniques may also be applied. Dichotomous outcome assessments will be analysed using logistic regression and paired dichotomous outcomes will be analysed using McNemar tests, or using logistic regression with random effects. Missing data is a potential source of bias and therefore the operation of multiple imputations will be used to address the issue of missing values. An analysis of the drop-out will be conducted to validate the complete case analyses.

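### IMR is delivered in groups of 10, but the sample size and the planned t-test make no allowance for correlation within IMR groups; any positive correlation raises the type I error above 0.05 and erodes the stated 0.8 power

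*Protocol article*

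**What the plan says.** Under 'The experimental intervention' the protocol article fixes the delivery format: "IMR will be implemented in group format with 10 patients assigned to each group and two IMR facilitators", in weekly sessions over nine months. Under 'The control group', controls receive usual care adapted to the individual, which may include psycho-education and group therapy.

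Under 'Power and sample size' the calculation begins: "We are planning a trial of the continuous response variable, GAF-F, from independent control and experimental participants with one control per experimental participant". It takes a standard deviation of 15 ("response within each participant group was normally distributed with a standard deviation of 15"), a 6-point difference ("conservatively estimate the true difference in the experimental and control group means to be 6 points on the GAF-F score"), power 0.8 and alpha 0.05 ("The type I error probability associated with this test of the null hypothesis is 0.05"), and arrives at 200 participants. No ICC or design effect appears.

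Under 'Data analysis' the method for continuous outcomes is: "The analysis of differences between groups will be conducted using t-tests", with ANOVA also named. Repeated measures techniques are mentioned as a possibility, and random effects only as an option for paired dichotomous outcomes. Neither refers to IMR groups. The limitations in the Discussion cover staff who work with both arms and incomplete blinding, but not the grouping of IMR participants.

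**The concern.** With 100 participants in the IMR arm and 10 per group, there are about 10 IMR groups. Members of a group share their peers, their two facilitators and the same nine months of sessions, so their outcomes may resemble each other more than those of participants in different groups. Controls have no such grouping imposed by the trial. This is a partially nested design.

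A t-test that treats all 200 observations as independent ignores the between-group component of variance in the IMR mean. If that component is positive, the standard error is too small, confidence intervals are too narrow and p-values too low. The error favours a false positive on the primary outcome, GAF-F at 9 months, and on the other continuous outcomes compared in the same way. A test that does allow for the groups has less power than the section states.

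**Working it through.** **Inputs from the protocol article.** Difference 6, SD 15, alpha 0.05, power 0.8, 1:1 allocation, total 200 (all from 'Power and sample size'); IMR group size 10 ('The experimental intervention'). The test is taken as two-sided, which reproduces the stated N.

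**Assumptions.** 10 full IMR groups (100/10); controls unclustered; total SD held at 15 in both arms; ICC from 0 to 0.10, because the article gives none.

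**Step 1: the plan's own figure.** n per arm = 2 × 15² × (1.960 + 0.842)² / 6² = 98.1, rounded up to 99, so 198 in total. The stated 200 reproduces. With 100 per arm, the SE of the difference is 15 × √(2/100) = 2.121 and power is Φ(6/2.121 − 1.960) = 0.807.

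**Step 2: allow for IMR groups.** The design effect in the IMR arm is DE = 1 + (10 − 1) × ICC. Then:

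- Var(difference) = (225/100) × DE + 225/100 = 2.25 × (1 + DE)
- Power from the clustered variance alone = Φ(6/SE − 1.960)
- Type I error of the ordinary t-test = 2 × [1 − Φ(1.960 × √(2/(1 + DE)))]
- n per arm for 80% power = 225 × (1 + DE) × (1.960 + 0.842)² / 36

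The last power column was simulated. It is a group-level test with Satterthwaite degrees of freedom: 10 IMR group means against 100 individual controls.

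| Assumed ICC | DE | SE | Type I error of t-test | Power, variance only | Power, small-sample df | Total N for 80% (variance only) |
|---|---|---|---|---|---|---|
| 0 | 1.00 | 2.121 | 0.0500 | 0.807 | about 0.78 | 198 |
| 0.01 | 1.09 | 2.169 | 0.0552 | 0.790 | 0.76 | 206 |
| 0.02 | 1.18 | 2.215 | 0.0605 | 0.773 | 0.74 | 214 |
| 0.05 | 1.45 | 2.348 | 0.0766 | 0.724 | 0.69 | 242 |
| 0.10 | 1.90 | 2.554 | 0.1036 | 0.651 | 0.61 | 286 |

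Simulation of the ordinary t-test under the null (40,000 trials per setting) gave 0.054, 0.060, 0.074 and 0.101 at ICC 0.01, 0.02, 0.05 and 0.10, in line with the formula.

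**Step 3: where power crosses 0.80.** Power of 0.80 needs SE = 6/2.802 = 2.142, so 2.25 × (2 + 9 × ICC) = 4.587 and ICC = 0.0043. There is almost no slack: on the variance alone, power drops below 0.80 once the ICC exceeds about 0.004.

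**Step 4: separate the two losses.** The last two power columns differ by about 2 to 4 points at every ICC, including zero. That part is the price of estimating between-group variance from only 10 groups. At ICC 0.01, clustering itself costs 1.7 points (80.7 to 79.0) and the degrees of freedom about 3 more.

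**The case against.** **No ICC is given.** A reader might infer that the trial's type I error is above 0.05 and its power below 0.8 as a matter of fact. The article does not support that. At ICC 0 the planned calculation and the t-test's type I error are both correct, and at 0.01 the departure is small. The claim has to be conditional, and it is written so here.

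**Centre is not a source.** A reader might also count a shared centre as part of the clustering. Randomisation is stratified by centre and diagnosis, so similarity due only to centre is balanced between arms. If the strata are prognostic, an unadjusted t-test is somewhat conservative, which offsets part of the inflation. The article gives no figure from which to size this.

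**The partly nested picture is idealised.** Usual care can include group therapy, and some facilitators are primary care providers for patients in both arms, so part of any staff effect is shared. Participants may also stop attending yet remain in follow-up, which would make the effective group smaller than 10. These points affect the size; they do not remove the correlation that shared sessions can produce.

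**The word 'independent' may only mean unmatched arms.** That is a fair reading, and the word need not be deleted. The calculation and the t-test still require independence within arms.

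**Not every outcome is affected in this way.** Dichotomous outcomes go to logistic regression, McNemar tests or random-effects models. The figures above apply only to continuous outcomes compared by t-test.

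**A full analysis plan may model the groups.** It may, and details such as the degrees-of-freedom method belong there. But the point is not missing detail: the article states a test and a power that leave the groups out. A later model would not change the basis of the stated 0.8.

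**Conclusion.** The point holds in conditional form. For any positive correlation within IMR groups, other things equal, the planned t-test exceeds its nominal 0.05. On the clustered variance alone, 200 participants give less than 0.8 power once the ICC exceeds about 0.004.

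Over an assumed ICC of 0.01 to 0.10 the type I error runs from 5.5% to 10.4%. Power runs from 79% down to 65% on the variance alone, or from 76% down to 61% for a valid small-sample test. The effect is modest at 0.01 to 0.02 and material from 0.05 upward; nothing in the article says which applies. The figures rest on 10 full groups of 10, unclustered controls, SD 15 and a true difference of 6.

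This should be fixed, because it touches the primary comparison and the remedy is cheap. The article does not establish that the trial's error rate is in fact inflated.

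**What to change.** 1. Under 'Data analysis', replace the t-test for GAF-F and the other continuous outcomes with a partially nested mixed model: a random intercept for IMR group in the IMR arm only, controls as singletons, and small-sample degrees of freedom (for example Satterthwaite or Kenward-Roger). Adjust for the stratification factors, diagnosis and centre.
2. Record each participant's assigned IMR group and analyse by that assignment whatever the attendance, in keeping with intention-to-treat.
3. Under 'Power and sample size', add a sentence on possible correlation within IMR groups and restate the power of 200 participants over a stated ICC range, for example 0 to 0.05. On the figures above that is 80.7% to 72% from the variance alone, or about 78% to 69% with small-sample degrees of freedom.

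N stays at 200 and the only added data item is the group identifier. The cost is somewhat wider confidence intervals and a less favourable power statement, including a loss of 2 to 3 points from the degrees of freedom even if the ICC turns out to be zero.
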